### Pregnancy Test

All subjects capable of becoming pregnant will be sent a pregnancy test in the study kit. Each participant will need to verbally confirm that they are not pregnant during the pre-sampling call based on the results of the pregnancy test. If a participant is unable to confirm that they are not pregnant or if they are pregnant, they will not be able to continue with the study.

## Randomization, Blinding, and Unblinding

All randomization procedures will be stratified to ensure balance within groups. After baseline, participants will be randomized within the secure database, REDCap. Randomization will occur using a stratified block-randomization procedure with small, random sized-blocks. Randomization will be stratified by self-reported cigarette dependence, sex, and ONP use history (ever vs. never). Randomization will be counterbalanced and will not be changed once it is complete.

Participants are not blinded to their study product(s) and are instead active participants in trialing their products.

## Subject Completion, Withdrawal, and Early Termination

Participants will be invited to complete a 29-week, fully-remote study involving baseline, sampling, switching, and observational phases. The participant timeline will be complete once the Observation Phase Survey and Debriefing Calls are complete. Participants have the option to withdraw at any point by expressing their desire to withdraw to study staff orally or in writing. Study staff will complete a withdrawal form to document this event. If at any point a participant becomes unable to complete study tasks per protocol (e.g., inconsistent responses reported on questionnaires; inability to provide iCO or survey responses; injury, illness, or medications that impair ability to accurately complete study measures; desire to quit tobacco use; or inappropriate behavior toward study staff), [name] reserves the right terminate a subject’s participation in the study based on their safety and ability to complete the protocol.

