Studies collecting data via smartphone and biomarkers remotely. Our team has considerable remote data collection experience using smartphones to complete follow-up assessments (11 studies, including one among rural Appalachian smokers) and Bedfont’s iCO device to collect exhaled carbon monoxide (CO) remotely (4 studies; e.g., U01DA045537). Importantly, these studies have helped us improve upon our participant instructions and troubleshooting procedures to maximize adherence. For example, we significantly improved adherence to the iCO device from 61% to 87% by simply modeling its use via video calls/conference (e.g., Zoom, FaceTime), in addition to written and pictorial instructions.

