**Data Analysis Techniques**

Power Analysis: Biochemically verified 7-day point prevalence abstinence from cigarettes at the end of the 12- week Switch Phase by study arm (ONP, NRT) is the primary outcome of the study and was chosen because it is a critical outcome to inform public health interventions and potential FDA regulations of ONPs. It is also stringent statistically, requiring a sample size that will provide sufficient statistical power to examine the other study outcomes. Although we will not biochemically confirm use of NRT or ONP, biochemical verification of abstinence from cigarettes combined with self-reported use of NRT or ONP is indicative of complete switching. To derive our NRT arm abstinence estimate of 13% we used our prior trial that investigated the effects of NRT sampling on cessation outcomes.^70^ Crucially, this trial included a sample of rural participants; in this rural subsample, the cessation rate was 13%.^70^ We derived our ONP arm estimate of 23% based on our preliminary data. As the goal of that study was not switching, we believe this estimate to be conservative. Assuming 80% retention at the end of the 12-week Switch Phase, a total sample of 800 participants (400 per arm), will provide greater than 95% power to detect a difference in smoking abstinence between the NRT and ONP arms for a two-sided, α=0.05 level chi-squared test. Further assuming 70% retention at the end of the 14-week Observation Phase, a sample of 700 (350 per arm) will provide over 90% power to detect a significant difference between the ONP and NRT arms.

Data Analytic Plan: Statistical analyses will be performed using SAS 9.4. P-values less than 0.05 will be considered statistically significant. Baseline demographics and smoker characteristics will be summarized by arm (ONP and NRT), as appropriate. Continuous variables will be presented as mean ± standard deviation and compared between the arms with t-tests. Categorical variables will be presented as frequencies and proportions and compared with chi-squared tests. Balance of all covariates according to randomization will be confirmed prior to conducting the below analyses. Any imbalanced covariates will be controlled for in regression models.

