Aim 3: Aim 3 will examine differences between the ONP and NRT arms in (H3a) abstinence from cigarettes, (H3b) number of days the study products are used, and (H3c) purchase and continued use of the study products during the 14-week Observation Phase. Hypothesis 3a: The analysis of abstinence from cigarettes at the end of the Observation Phase will mirror that of hypothesis 1b and will be evaluated with a logistic regression model. Hypothesis 3b: Linear regression analysis will be used to compare the number of days the products are used during the Observation Phase between the ONP and NRT arms; a normalizing transformation will be employed if needed and appropriate baseline characteristics will be adjusted for. Hypothesis 3c: The continued purchase and use of either ONP or NRT after during the 14-week Observation Phase will be compared between the arms with logistic regression analysis, adjusting for all appropriate confounders. Missing Data: In the event of missing data, we will contact participants immediately. If a participant drops out, we will attempt to gather follow-up information by calling and trying to reach the participant through other provided contact information. However, if a participant refuses to be contacted or loses contact with the investigators, we will censor data at point of loss. Two statistical approaches will be used to handle missing data. First, we will use inverse probability weighting with propensity scores. This is a two-step procedure in which we first model the probability of missingness as a function of baseline covariates and previous outcomes. Next, the inverse of the resulting predicted probabilities (from the logistic regression model) will serve as weights in our proposed model of the response. We will compare these results to a more conservative intent-to-treat approach as a final step.

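### The discretionary termination rule covers problems with surveys and iCO tests, the instruments of the primary outcome, and does not secure week-12 follow-up afterwards

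*Protocol*

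**What the plan says.** Protocol section 3, Subject Completion, Withdrawal, and Early Termination, opens the rule with "If at any point a participant becomes unable to complete study tasks per protocol". Its examples include "inconsistent responses reported on questionnaires; inability to provide iCO or survey responses". The investigator then "reserves the right terminate a subject’s participation in the study based on their safety and ability to complete the protocol". What ends is participation in the study, not only the supply of product.

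Section 15, Data Analysis Techniques, makes the primary outcome "Biochemically verified 7-day point prevalence abstinence from cigarettes at the end of the 12- week Switch Phase". It is built from the post-switch survey and an exhaled CO reading of at most 6 ppm (section 3, Switch Phase and Obtain exhaled iCO). The same instruments are used earlier, at the end of the Sampling Phase and at week 6 of the Switch Phase.

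Other parts of the protocol aim at keeping data. The Switch and Observation Phase sections provide for up to 10 contacts when a survey is outstanding. The missing-data text in section 15 says "In the event of missing data, we will contact participants immediately", attempts to follow up dropouts, and censors a participant who refuses contact or is lost. It then plans inverse probability weighting on baseline covariates and previous outcomes, compared with an intent-to-treat approach. The note in section 5, Inclusion/Exclusion Criteria, defines the intent-to-treat sample by baseline completion, iCO of 7 ppm or more at the pre-sampling call, and confirmation of not being pregnant.

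Participants know their product (section 3, Randomization, Blinding, and Unblinding). The protocol describes no blinding of the person who decides on termination.

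**The concern.** The two data-quality grounds concern the measurements from which the primary outcome is made. A participant who has trouble with a survey or an iCO test at the end of sampling or at week 6 may still be able to give a valid week-12 result. The rule allows that person to be removed first, and the protocol does not say that the week-12 survey and iCO are still requested.

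Trouble with smoking questionnaires and CO tests is plausibly related to whether someone is smoking. The decision is discretionary, comes after randomisation, and can be made with knowledge of arm. This combination can produce missing outcomes that depend on the outcome and differ between arms. What is at stake is mainly bias in the primary comparison rather than power. An analysis plan can choose how to code such cases, but it cannot recover an outcome that was never collected.

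**Working it through.** **1. The plan's own figure.** Inputs from section 15: 13% (NRT) and 23% (ONP), 400 per arm at week 12, two-sided α = 0.05.

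- Mean proportion: (0.13 + 0.23)/2 = 0.18.
- Standard error under no difference: √(2 × 0.18 × 0.82/400) = 0.02717.
- Standard error under the alternative: √((0.13 × 0.87 + 0.23 × 0.77)/400) = 0.02694.
- z = (0.10 − 1.96 × 0.02717)/0.02694 = 1.736, so power is 95.9%.

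With 350 per arm the same formula gives 93.3%. Both stated figures (above 95% and above 90%) are confirmed.

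**2. The passages side by side.**

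| Step | What the protocol provides |
| --- | --- |
| Survey outstanding | Up to 10 contacts |
| Participant drops out | Follow-up attempted; censored on refusal or loss of contact |
| Doubtful record | Flagged for review and correction (section 10) |
| Investigator ends participation over survey or iCO problems | No threshold; no statement that week-12 or observation outcomes are still requested |

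A participant terminated by the investigator has neither refused contact nor been lost, so the censoring rule does not describe this case.

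**3. Assumed illustration of bias.** The protocol gives no termination rate. Assume no true difference, 18% abstinent in both arms (the midpoint above), 400 observed per arm, and no weighting. Remove a fraction f of one arm only, all of them smokers.

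- Abstainers in that arm: 0.18 × 400 = 72, unchanged.
- Apparent rate: 72/(400(1 − f)).
- SE₀ is the pooled and SE₁ the unpooled standard error of the difference d. Type I error = Φ((d − 1.96 SE₀)/SE₁) + Φ((−d − 1.96 SE₀)/SE₁).

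| f | Apparent rate | d | SE₀ | SE₁ | Two-sided type I error |
| --- | --- | --- | --- | --- | --- |
| 5% | 72/380 = 18.9% | 0.0095 | 0.0278 | 0.0278 | 0.053 + 0.011 = 6.4% |
| 10% | 72/360 = 20.0% | 0.0200 | 0.0285 | 0.0285 | 0.105 + 0.004 = 10.9% |

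With 13% in both arms instead, the errors are 5.9% and 9.0%.

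**4. Removal that is equal in both arms.** If 10% of each arm is removed and all are smokers, 13% and 23% become 0.13/0.90 = 14.4% and 0.23/0.90 = 25.6%. The difference is 11.1 points instead of 10.

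**5. Power.** Extra terminations unrelated to arm or outcome cost little: 5% leaves 380 per arm and 95.0% power, and 10% leaves 360 per arm and 93.9%.

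**The case against.** The rule is discretionary and speaks of inability to complete study tasks. Outstanding surveys are chased repeatedly, and the incentive scheme pays per survey with a bonus for completing all five, which implies that people who miss some stay enrolled. Termination does not take anyone out of the intent-to-treat sample. Weighting on previous outcomes could use week-6 smoking status. If the intent-to-treat analysis counts missing as smoking, it restores 72/400 in both arms of the illustration. An investigator in a fully remote, paid study also has reason to want some discretion over unreliable responders.

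Much of this stands, and it rules out three stronger readings that a reader might infer.

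- **That one missed interim test ends participation.** The text does not say so; a single miss is only not excluded, for want of a threshold.
- **That an abstinence claim contradicted by CO becomes missing.** The listed ground is inconsistency on questionnaires, and a CO reading is not a questionnaire response. CO above 6 ppm already fails the verified endpoint, and a contradiction at week 12 exists only once both values are recorded.
- **That the iCO adherence history gives a termination rate.** The statement "we significantly improved adherence to the iCO device from 61% to 87" percent is not described as a rate per session, and everyone in the intent-to-treat sample has already completed an iCO reading.

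The objection does not supply the missing outcome. Weighting on recorded data cannot be relied on to capture a staff decision. Counting missing as smoking would misclassify a terminated participant who would have been abstinent at week 12. The protocol does not state how its intent-to-treat approach codes these cases; that may be in an analysis plan not shown and is not criticised here.

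**Conclusion.** The point holds in limited form. The protocol states a termination rule, open to discretion at any time in an open-label trial, on grounds tied to the outcome instruments. It sets no threshold and does not secure week-12 collection afterwards, so it can create missing primary outcomes related to smoking status.

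The size is unknown. Type I error of about 6% or 11% follows only if smokers equal to 5% or 10% of one arm alone are removed, with 18% abstinence in both arms, 400 per arm and no weighting. Nothing in the protocol shows that removal would be this frequent or this one-sided. The stated power is correct. This is a cheap improvement to the design, not a flaw that invalidates the trial.

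**What to change.** In section 3, Subject Completion, Withdrawal, and Early Termination, limit the two data-quality grounds to flagging the record for review, in line with the quality-control process in section 10. Then add a statement along these lines: missed or inconsistent assessments do not in themselves end participation; the week-12 and observation surveys and iCO tests are still requested from everyone in the intent-to-treat sample defined in section 5, unless the participant withdraws consent; and a missed or inconsistent interim assessment affects only that time point. The safety and conduct grounds in the same sentence are not part of this point and can stay as they are.

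The cost is a change to one passage of the protocol, plus continued reminders and per-survey payments for poor responders. No new procedure is needed.

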The Post-sampling Survey will assess participants’ confidence in switching to their study product, as well as their experiences and extent of sampling during the Sampling Phase ***(Survey Message, Post-Samp Survey****)*. The post-sampling survey will be sent on day 10 after the sampling phase starts. The survey will be completed prior to the Post-Sampling Call. Study staff will call, email, or text (any combination based on participant preferences) participants up to 10 times to remind them to complete the survey if they have not completed it within two weeks. ***(Survey reminder).***

Sampling Phase: Post-sampling Call

The Post-sampling Call will be one to two days before the participant’s switch date. Study staff will confirm receipt of additional products, remind participants of their switch date and that upon waking the morning of their Switch Date they should not smoke cigarettes. They will be instructed to stop smoking and continue with their allocated study product (ONP or NRT) for 12 weeks. Staff will also answer any product use questions and provide troubleshooting as needed. ***(Post-Samp Call Script)*** If study staff are unable to connect with the participant, the participant will be emailed or texted the information ***(Post-Samp Email).***

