3. Our accompanying brochures will discuss the anticipated negative consequences of nicotine intoxication (nausea, headache) and advise participants to discontinue one or both products should they arise. We will track adverse events at every study contact and will have a toll-free number available for participants to call if they experience an adverse event (AE). All study contacts will remind participants of this number. Participants will be encouraged to contact Drs. [name] or [name] as soon as possible for serious events. If they wish, they may contact their local MD. We will withdraw participants who have a serious AE, become pregnant, or begin breastfeeding. For other AEs, if the participant’s physician or the participant wishes it, the participant will be withdrawn from the study. We will assess dependence on all products used, and for participants whose dependence increases for any product without a corresponding decrease >50% in CPD, we will refer them to seek treatment for tobacco dependence.

4. Use of ONPs/NRT among non-participants and non-smokers, including children: We will strongly advise participants that they are not to share the study product with others, and that they should store the product in a secure area that is out of reach of children and pets.

5. Confidentiality: We will use the participant’s name only in the screening and participant phone calls. All other references to participant data will be under a code. All database files will include password protection to further ensure confidentiality. We do not expect this study to present greater risks than other studies our team has conducted and expect to continue treating participant data with the utmost respect and confidentiality.

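### A wish to quit tobacco is a discretionary ground for ending participation after randomisation, although stopping cigarettes is the primary outcome, and follow-up of those terminated is not secured

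*Protocol*

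**What the plan says.** Protocol Section 3, Subject Completion, Withdrawal, and Early Termination, opens the power to terminate with "If at any point a participant becomes unable to complete study tasks per protocol". It then gives examples, among them "inability to provide iCO or survey responses" and "desire to quit tobacco use; or inappropriate behavior toward study staff". In these cases the study lead "reserves the right terminate a subject’s participation in the study based on their safety and ability to complete the protocol". The power concerns participation in the study, not only use of the product, and no text confines it to the time before randomisation.

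Other sections point the other way:

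- Section 3, Sampling Phase, on the call before the switch date: "They will be instructed to stop smoking and continue with their allocated study product (ONP or NRT) for 12 weeks".
- Section 3, Observation Phase: at the debriefing call, continuing smokers are advised to quit, and those who have switched are sent material on giving up nicotine altogether.
- Section 15, Data Analysis Techniques, on the main endpoint: "Biochemically verified 7-day point prevalence abstinence from cigarettes at the end of the 12- week Switch Phase by study arm (ONP, NRT) is the primary".

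On missing data, Section 15 says that staff will try to reach participants who drop out, and that data are censored when a participant refuses contact or cannot be found. The analysis then weights by the inverse of a probability modelled on baseline covariates and earlier outcomes, and compares the result with an intent-to-treat approach. Participants terminated by staff are not mentioned.

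**The concern.** A rule for ending participation is harmless to the comparison when it has nothing to do with the outcome. This one does: a wish to quit tobacco plausibly goes with stopping cigarettes, which is what the trial measures. If such people are terminated and not followed up, likely successes turn into missing values, or into smokers if missing is scored that way. The decision rests with staff, the section gives no criteria for it, and participants are not blinded (Section 3, Randomization, Blinding, and Unblinding). The phrase may also be read differently by arm, since Section 1 describes ONPs as marketed and regulated as tobacco products and NRT is an approved aid to quitting. Use of the ground at equal rates would mainly shrink the difference between arms. Unequal use could shift it in either direction.

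**Working it through.** **1. The texts side by side.** Take a participant who, in week 5 of the Switch Phase, says that they want to be free of all tobacco and nicotine.

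- Under the termination section, the study lead may end their participation.
- Under the Sampling Phase instruction, they are doing half of what was asked (no cigarettes) and may or may not continue the product.
- Under the primary outcome, if they have not smoked for 7 days at week 12 and the iCO reading agrees, they are a success. Use of the study product is needed only for complete switching (H1a).
- Under the note to the eligibility table in Section 5, they remain in the intent-to-treat sample, which is fixed by baseline completion, iCO of at least 7 and non-pregnancy. Their week-12 outcome is therefore needed.
- Under the missing-data text, it is unclear whether staff would try to obtain that outcome.

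**2. The plan's own figure.** Inputs from Section 15: 13% with NRT ("To derive our NRT arm abstinence estimate of 13% we used our prior trial"), 23% with ONP, 400 per arm, two-sided alpha 0.05, chi-squared test.

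Power = Φ{[d − 1.96·√(2p̄(1−p̄)/n)] / √([p₁(1−p₁)+p₂(1−p₂)]/n)}, with d = 0.10 and p̄ = 0.18.

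- n = 400: (0.10 − 1.96 × 0.02717)/0.02694 = 1.736, power 95.9%.
- n = 350: (0.10 − 1.96 × 0.02904)/0.02880 = 1.496, power 93.3%.

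Both stated powers (above 95% and above 90%) are reproduced. They are not in dispute.

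**3. Illustration with no true difference.** The document gives no removal fraction, so every input here is an assumption: true abstinence p = 18% in both arms (the mean of 13% and 23%), and a fraction f of abstainers removed from one arm only. The rate in that arm is p(1−f) if the removed are counted as smoking, and p(1−f)/(1−pf) among those observed.

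| f | Counted as smoking | Gap | Among those observed | Gap |
|---|---|---|---|---|
| 10% | 18 × 0.90 = 16.2% | 1.8 points | 16.2/98.2 = 16.5% | 1.5 points |
| 20% | 18 × 0.80 = 14.4% | 3.6 points | 14.4/96.4 = 14.9% | 3.1 points |

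With f = 20% in one arm, 400 per arm before removal and a common true rate of 13% to 23%, the test among those observed rejects in about 17% to 25% of trials instead of 5%.

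**4. Illustration under the design effect (13% vs 23%, 400 per arm before removal).**

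| Assumed removal of abstainers | Observed: difference, power | Counted as smoking: difference, power |
|---|---|---|
| 10% in both arms | 9.3 points, 94.2% | 9.0 points, 93.4% |
| 20% in both arms | 8.6 points, 91.9% | 8.0 points, 89.8% |
| 20% in ONP only | 6.3 points, 66.7% | 5.4 points, 55.6% |
| 20% in NRT only | 12.3 points (inflated) | 12.6 points (inflated) |

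**5. Would the planned analysis repair it?** Weighting is valid if, given the variables in the missingness model, termination is unrelated to the outcome. A wish to quit that arises during the Switch Phase is neither a baseline covariate nor an earlier outcome, so weighting corrects for it only as far as those variables happen to predict it. The intent-to-treat comparison still needs a value for each terminated participant.

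**The case against.** The strongest reply is that this is loose wording rather than a flaw in design. Termination is discretionary, and the list illustrates inability to carry out study tasks. One of those tasks is to keep using the allocated product. Since ONPs are classed as tobacco products, and Section 12 says that quitting tobacco products is not a study objective, the phrase may mean wanting to give up the study product as well. That reading is fair, and it means that the sections do not flatly contradict each other. It does not remove the problem, because a person who gives up everything is still abstinent from cigarettes. The entry exclusion for people seeking cessation treatment does not help either: it is a screening rule, while this power applies at any point.

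Some stronger readings are tempting, but the document does not support them:

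- *That would-be quitters are removed as a rule.* The text only reserves a right, and nothing suggests frequent or unequal use.
- *That missed surveys or iCO tests end participation.* The ground is inability to provide them, and late surveys lead to up to 10 contacts.
- *That stopping the product ends outcome assessment.* Stopping the product is not on the list, and the advice in Section 13 to stop a product because of symptoms is not itself tied to leaving the study.
- *That follow-up stops for everyone who leaves.* Section 15 promises attempts to reach those who drop out. The gap is that it does not clearly include people whom staff terminate.
- *That safety data after a serious event are lost.* Section 13 says "We will withdraw participants who have a serious AE, become pregnant, or begin breastfeeding". That is a separate safety rule with its own reporting arrangements, and it is not part of this point.

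**Conclusion.** The concern holds in a limited form. A ground related to the primary outcome can end participation after randomisation, and the protocol does not say that outcomes are still sought from people so terminated. Neither the size nor the direction of any bias can be derived from the document. The gaps of 1.8 to 3.6 points (counted as smoking) or about 1.5 to 3.1 points (observed) rest on an assumed 18% abstinence in both arms and on removal of 10% to 20% of abstainers from one arm only. Removal of 10% in both arms would leave power at 93% to 94%, so modest and even-handed use would do little harm. The reason to act is that the risk is easily avoided, and that no analysis can restore outcomes that were not collected.

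**What to change.** Reconcile the termination section with the Sampling Phase instruction, the Observation Phase debriefing, the primary outcome and the missing-data text:

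1. Remove the wish to quit tobacco as a ground for ending participation after randomisation, or state that it does not end outcome follow-up.
2. State in Section 15 that the follow-up attempts also apply to randomised participants in the intent-to-treat sample whom staff terminate. They would still receive the week-12 and end-of-Observation survey and iCO requests.
3. State that these participants are analysed in their assigned arm unless they withdraw consent to follow-up.

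Decisions about product use stay as they are. The cost is a short amendment, plus a few more surveys and incentives.
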